#### Uni- & bivariate analysis

The percentage of patients with a positive response will be calculated post-treatment and at 9 months after treatment and differences between the three randomisation arms will be tested with the chi-square test.

In addition, the adequate relief scores and secondary outcomes (IBS- SSS, IBS-QoL, SCL-90-, CS- FBD-, SES- and TiC-P scores) will be estimated by time point of assessment and arm of randomisation using a statistical model for repeated measurements (preferably a random effects model). To assess the difference between the arms of randomisation by time point of assessment, terms for interaction of {arm × time point} will be included in the statistical model.

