### Design

The study is designed as a comparative and a non-inferiority 12-weeks single blind controlled parallel-group trial. The trial will involve IBS patients in primary and secondary care, who will be randomly allocated to either 6 sessions of individual hypnotherapy, 6 sessions of hypnotherapy in group format, or 6 sessions of educational supportive therapy in a group format (control condition) (Flowchart Figure 1). Starting May 2011, the inclusion of patients will take approximately two years, with a follow-up of nine months.

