#### Main study parameter/endpoint

In line with previous conclusions on optimal outcome assessment in trials on functional gastrointestinal disease [23,24], we chose the number of weeks with adequate symptom relief as the primary outcome. This measure addresses weekly symptom improvement in IBS with treatment using a single question ("Did you have adequate relief of IBS-related abdominal pain or discomfort in the past week?") scored on a dichotomous scale (Yes/No). This instrument is a well validated simple outcome assessment for IBS treatment [25] with a positive responder being defined as someone with more than 2 weeks adequate relief per month [26] which has determined to indicate a clinically significant improvement [26].

The first primary outcome is the difference in the percentage of positive responders between group hypnotherapy and group educational therapy. Group hypnotherapy is expected to be substantially more effective than educational therapy.

The second primary outcome is the difference in percentage of positive responders between group hypnotherapy and individual hypnotherapy. Group hypnotherapy is expected not to be inferior to individual hypnotherapy.

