### Sample Size Calculation

Assuming an individual hypnotherapy response rate of 57% [2], a maximum acceptable level of difference of 15% between individual and group hypnotherapy, an alpha of 0.05 and power (1-beta) of 0.80, 135 patients are required in both arms of the non-inferiority trial to show that group-hypnotherapy is not inferior to individual hypnotherapy.

Spiller [34], in an overview of 25 randomised controlled trials, states that when the placebo response is plotted against the length of study, placebo response will be maximum of 75% at around 6-8 weeks, falling to 25% at 24 weeks and zero at 12 months. Our follow-up period will be 9 months. To test whether group hypnotherapy is more effective than group placebo therapy, we will have more than sufficient power assuming a placebo-response rate of 25% and a group hypnotherapy response rate of 57% [13] using the proposed 135 patients in both arms. Powering the study for only the comparison between hypnotherapy and the control intervention, would require only 44 patients in both arms assuming an alpha of 0.05, a power (1-beta) of 0.80, a cluster size of 6 patients per therapist and an intra-class correlation coefficient of 0.05. Assuming at least 10% of loss to follow-up, 354 patients need to be included in the study (150+150+54 (placebo-arm)).

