### Statistical analysis

#### General remarks

All statistical analyses will be based on the intention-to-treat principle, i.e. patients will be analysed according to their initial assignment to one of the randomisation arms.

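### The non-inferiority outcome is given only a chi-square test of difference, and the 15-point margin used to size the trial is never applied in the analysis

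*Protocol article*

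**What the plan says.** The Design section of the protocol article states that "The study is designed as a comparative and a non-inferiority 12-weeks single blind controlled parallel-group trial".

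Under Main study parameter/endpoint there are two primary contrasts in the percentage of positive responders:
- Superiority: "The first primary outcome is the difference in the percentage of positive responders between group hypnotherapy and group educational therapy".
- Non-inferiority, group against individual hypnotherapy: "Group hypnotherapy is expected not to be inferior to individual hypnotherapy".

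The Sample Size Calculation takes 57% response on individual hypnotherapy and "a maximum acceptable level of difference of 15% between individual and group hypnotherapy". With "an alpha of 0.05 and power (1-beta) of 0.80, 135 patients are required in both arms of the non-inferiority trial", it arrives at the size of the two large arms.

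Under Uni- & bivariate analysis, the responder percentage is to be computed after treatment and at 9 months, and "differences between the three randomisation arms will be tested with the chi-square test". A repeated-measures model with arm-by-time interaction terms is added, again to assess the difference between arms. Neither that section nor the rest of the analysis text mentions the margin, a confidence interval, a non-inferiority criterion or a pairwise contrast.

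**The concern.** The article does not leave the test open. It names one, and that test does not fit one of the two primary questions. A chi-square test takes equality as its null hypothesis. Failing to reject equality is not evidence that group therapy is less than 15 points worse, and rejecting it does not show by how much the arms differ.

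The claim at stake is the main practical one: the abstract's Discussion says that group treatment could be offered to more patients at lower cost if the two formats do not differ in efficacy.

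A second, weaker issue depends on how the sentence is read. If one test covers all three arms, a significant result does not say which arms differ, so it does not answer the superiority question for group hypnotherapy either.

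**Working it through.** **Inputs from the protocol article.** Individual response 57%, margin 15 points, alpha 0.05 (sidedness not stated), power 0.80, 135 per hypnotherapy arm; control response 25%; allocation 150 + 150 + 54 with 10% loss (all from Sample Size Calculation). A placebo response of 37.5% comes from the Placebo effect section.

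**Assumptions.** 48 or 49 evaluable controls (54 × 0.9 = 48.6). No clustering in the simulations. Simulations use 400,000 binomial runs, Pearson chi-square at 0.05 and Wald limits for the risk difference.

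**Step 1. Reproduce 135.** With 57% in both arms:

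n = (z(1−α) + z(0.80))² × 2 × 0.57 × 0.43 / 0.15²

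- One-sided α = 0.05: (1.645 + 0.842)² × 0.4902 / 0.0225 = 134.7, so 135. This matches.
- One-sided α = 0.025: (1.960 + 0.842)² × 0.4902 / 0.0225 = just over 171.0, so 172.

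Allowing for loss, 135 / 0.9 = 150, as stated. The trial is therefore sized for a one-sided 5% test against a 15-point margin, with no design effect. The chi-square is a different test.

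**Step 2. The three-arm test and the second primary question.** Response rates are in the order individual / group / control, with 135/135/48 evaluable.

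| True rates | Three-arm chi-square significant | Margin test (one-sided 0.05) declares non-inferiority |
|---|---|---|
| 57 / 57 / 25 (formats equal) | 97.5% | 79.5% |
| 57 / 42 / 25 (group worse by the full margin) | 96.5% | 4.6% |

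The control arm drives the three-arm result. The test behaves almost identically in the two situations that the second question has to separate.

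**Step 3. A pairwise test and the second primary question.** At 57% versus 42% with 135 per arm:

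SE = √[(0.57 × 0.43 + 0.42 × 0.58) / 135] = 0.0602

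P(not significant) ≈ 1 − Φ(0.15 / 0.0602 − 1.96) = 1 − Φ(0.53) ≈ 0.30

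Simulation gives 0.319. The margin-based test errs 4.6% of the time at the same point.

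A single data set shows the gap. Take 77/135 (57.0%) individual and 65/135 (48.1%) group:
- Difference −8.9 points; chi-square p = 0.14.
- SE = √[(0.5704 × 0.4296 + 0.4815 × 0.5185) / 135] = 0.0605.
- Lower one-sided 95% limit: −8.9 − 1.645 × 6.05 = −18.8 points. Non-inferiority fails although the chi-square is not significant.

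With truly equal formats at 57%, about 18% of trials would be non-significant and yet fail non-inferiority.

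**Step 4. The first primary question, only if the test is the three-arm one.** At 57 / 37.5 / 37.5 with 135/135/49, group equals control, yet the three-arm test is significant about 88% of the time. The pairwise group-versus-control chi-square rejects 4.9% of the time there, and has about 98% power at 57% versus 25%.

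**Step 5. Power of the margin-based analysis at 135 per arm, 57% in both.** SE = √(0.4902 / 135) = 0.0603.
- One-sided 0.05: Φ(0.15 / 0.0603 − 1.645) = 0.80 (simulation 0.795).
- One-sided 0.025: Φ(0.15 / 0.0603 − 1.960) = 0.70 (simulation 0.71).

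**The case against.** The strongest reply is that the differences between three arms can be read as pairwise tests, since the endpoint section already fixes the two pairs. That reading is open: the text never says overall or omnibus. Under it, group versus control gets a standard superiority test with the right error rate and ample power (Step 4, ignoring clustering). A reader might infer that both primary hypotheses fail; the document does not support that, because the first is affected only under the three-arm reading. The second is affected under either.

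A reader might also infer that the trial will treat a non-significant result as proof of equal efficacy. No passage says so, and the article states a non-inferiority design with a maximum acceptable difference. The 32% is therefore conditional on that misreading. What stands without it is that the named test cannot answer the question.

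A third temptation is to fault the statement that "All statistical analyses will be based on the intention-to-treat principle", because non-attendance could draw the two hypnotherapy arms together. This is not an error. Intention-to-treat is a legitimate analysis set, the document gives no non-attendance rate, and a deficit diluted to within the margin is truly non-inferior for the intention-to-treat effect.

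Finally, one may say that such detail belongs in a statistical analysis plan. That would answer an omission, but here a test is stated and it does not match the hypothesis or the sizing.

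**Conclusion.** The point holds and must be fixed. The method stated for the responder rate does not test the second primary hypothesis under any reading, and the margin on which the trial was sized plays no part in the analysis. The potential cost is a false claim of non-inferiority about 32% of the time instead of about 5% when group therapy is worse by the full 15 points, should non-significance be read as equal efficacy. Failure to isolate group hypnotherapy from control is an ambiguity to clear up, not an established error.

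These figures rest on 57% response with individual therapy, 135 evaluable per hypnotherapy arm, 48 or 49 controls and independent patients. The sample size is not in question here: 135 reproduces, provided that alpha is one-sided 0.05.

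**What to change.** In Uni- & bivariate analysis, replace the chi-square sentence as the primary analysis by two named comparisons of the responder percentage:

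1. Group hypnotherapy versus educational supportive therapy: test of difference, with the risk difference and its two-sided 95% confidence interval.
2. Group minus individual hypnotherapy: risk difference, with non-inferiority concluded only if the lower one-sided 95% limit (the lower end of a two-sided 90% interval) is above −15 points.

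State the one-sided 0.05 in the Sample Size Calculation as well, so that sizing and analysis agree. Any three-arm chi-square can stay as descriptive. A per-protocol analysis may be added as a sensitivity analysis, but the correction does not require it.

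The cost is a change of wording, with no new data or patients. That holds only for the one-sided 5% level: judging non-inferiority on a two-sided 95% interval would leave about 70 to 71% power at 135 per arm, and 172 evaluable per arm would be needed for 80%.

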##### Costs

The Trimbos/iMTA Questionnaire (Tic-P) for costs associated with Psychiatric Illness, measures direct medical costs due to health care utilization during the past four weeks and indirect non-medical costs due to productivity loss during the past two weeks[33]. It can be adapted for other conditions as well and for this study was adapted for IBS.

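### TiC-P costs share the symptom scales' random-effects model; with about 135 v 49 evaluable patients, a common-variance fit would give too narrow a cost interval against control if hypnotherapy lowers costs

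*Protocol article*

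**What the plan says.** Under Uni- & bivariate analysis, one sentence covers "the adequate relief scores and secondary outcomes (IBS- SSS, IBS-QoL, SCL-90-, CS- FBD-, SES- and TiC-P scores". The end of that list runs straight into the method: "SES- and TiC-P scores) will be estimated by time point of assessment and arm of randomisation using a statistical model for repeated measurements", with the stated preference "preferably a random effects model". Arm-by-time interaction terms carry the treatment comparison. No other method for costs appears in the article.

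Under Costs, the TiC-P is described as an instrument that "measures direct medical costs due to health care utilization during the past four weeks and indirect non-medical costs due to productivity loss". The recall window is four weeks for health care use and two weeks for lost productivity.

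Under Time line and follow-up, secondary endpoints are measured three times: before treatment, straight after it, and 9 months later.

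Under Sample Size Calculation, the allocation is deliberately unequal: "354 patients need to be included in the study (150+150+54 (placebo-arm", after allowing for at least 10% loss to follow-up.

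**The concern.** The other instruments in the list are bounded scales, for which a single residual variance is often tolerable. Costs over a few weeks are different. They cannot be negative, they usually contain many zeros and a long right tail, and their spread tends to grow with their mean.

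That matters here because the control arm is about a third the size of each hypnotherapy arm. If hypnotherapy lowers costs, the small control arm has the larger variance. A variance shared across arms is then estimated mainly from the two large, cheaper arms, and the standard error for a contrast with control comes out too small. The error runs in one direction: precision is overstated when there is a true saving, and understated when hypnotherapy costs more.

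IBS-related costs are a secondary objective under Aims, and the end of Background describes the trial as comparing costs with a control intervention. An over-precise interval would therefore bear on a stated result, though not on the primary outcome.

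**Working it through.** **Evaluable numbers.** The non-inferiority size reproduces at one-sided 0.05: (1.645 + 0.842)² × 2 × 0.57 × 0.43 / 0.15² = 134.7, so 135 per arm. Then 135 / 0.9 = 150, and 54 × 0.9 = 48.6, about 49 controls. The total is 150 + 150 + 54 = 354.

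**Assumptions (not in the documents).** Control costs have SD 1 (units cancel) at all three assessments. Hypnotherapy costs have SD 1 at baseline and SD r at both follow-ups, where r is the ratio of mean costs to control. Within-patient correlation ρ is 0.3 or 0.6. The model is a random intercept with arm-by-time terms and variances common to all arms.

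**Formula.** Approximate coverage = 2Φ(1.96k) − 1, where k² = variance reported by the model / true variance. Let D = 1/135 + 1/49 = 0.027816.

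- 9-month difference: reported S × D, with S = [270(1 + 2r²)/3 + 49]/319; true r²/135 + 1/49.
- Change from baseline to 9 months (the arm-by-time contrast): reported 2E × D, with E = [270g + 49(1 − ρ)]/319 and g = (1 + 2r²)/3 − ρ(2r + r²)/3; true (1 + r² − 2ρr)/135 + 2(1 − ρ)/49.

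**Example, costs halved (r = 0.5).**

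- 9-month difference: S = (270 × 0.5 + 49)/319 = 0.5768. Reported 0.016044, true 0.022260, k = 0.849, coverage 90.4%.
- Change contrast, ρ = 0.3: g = 0.375, E = (270 × 0.375 + 49 × 0.7)/319 = 0.4249. Reported 0.023639, true 0.035608, k = 0.815, coverage 89.0%.

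| Hypnotherapy costs v control | 9-month difference | Change contrast (ρ = 0.3 to 0.6) |
|---|---|---|
| equal | 95.0% | 95.0% |
| 20% lower | 93.4% | 92.8-92.9% |
| 30% lower | 92.5% | 91.5-91.8% |
| 40% lower | 91.5% | 90.2-91.0% |
| 50% lower | 90.4% | 89.0-90.3% |
| 20% higher | 96.2% | 96.7% |
| 50% higher | 97.3% | 98.3% |

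**Simulation.** The formula ignores skewness. Simulating the three-arm, three-assessment design (gamma or lognormal costs, CV 1-2, 3,000 runs per setting) gave 92.5-94.5% at a 20% reduction and 90-91% at 50% for the 9-month difference. For the change contrast it gave 92-94% and 88-90%. A spot check with a fitted mixed model at a 50% reduction gave 88% (120 runs). A further simulation that also included settings with 30% zero costs gave 88-93% for the change contrast and 90-94% for the 9-month difference, with about 94-96% at equal means.

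**How much is imbalance?** With three equal arms of 106, the 9-month difference returns to about 95-96%. The change contrast stays at about 92-94%, because variance that shifts over time also misfits a random-intercept model.

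**Effect of the fix.** With arm-specific residual variances in the same example (r = 0.5, ρ = 0.3), the change contrast has reported variance 2 × 0.375/135 + 1.4/49 = 0.034127. Then k² = 0.034127/0.035608 = 0.958 and coverage is 94.5%. In simulation, arm-specific variances gave about 94-96% for the change contrast. For the 9-month difference they gave about 91-95% with gamma costs, falling to about 88-90% for lognormal costs with CV 2 and costs halved, where skewness with 49 controls remains.

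**The case against.** The strongest reply is that the article does not fix a normal, common-variance model. The same sentence covers adequate relief, a yes/no item, so the error distribution and variance structure are open, and an analysis plan not shown may settle them. That stands, and it makes the coverage figures conditional. It does not remove the point: the article names a model for costs, chosen jointly with the symptom scales, and a default fit of that model has one variance across arms.

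Four stronger readings are tempting and are not supported.

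- *Coverage falls to the mid-80s.* A two-arm, single-assessment calculation gives 90.5% at a 30% reduction and 85.8% at 50%. Sharing one variance across three arms at each follow-up separately gives 91.4% at 20% and 81.5% at 50%. Neither is the random-effects model that the article prefers, applied to three arms and three assessments.
- *The case for cheaper group treatment is undermined.* The lower-cost argument in the abstract's Discussion concerns group v individual hypnotherapy. Those arms are equal in size, so the imbalance mechanism is absent.
- *False savings become more likely.* With no cost difference, coverage stays at about 95%, so the test of no difference keeps its level. Nor does the article predict that controls will cost more.
- *Productivity loss gets half its weight.* The recall windows do differ ("indirect non-medical costs due to productivity loss during the past two weeks", against four weeks for health care), but no passage plans an unscaled total.

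**Conclusion.** The concern holds in a limited, conditional form. The article assigns TiC-P costs to the symptom scales' model with no allowance for variance that rises with the mean, in a trial with about 135 v 49 evaluable patients for each contrast with control. A common-variance version would have a real non-coverage rate of about 6-12% instead of 5% if hypnotherapy lowers costs by 20-50%. This assumes CV 1-2 and SD proportional to the mean; the documents supply no cost mean, SD or expected saving. If variance rose more slowly with the mean, the loss would be smaller. The point concerns interval width for one secondary outcome and leaves the primary analysis untouched, but it is worth correcting because the correction is nearly free.

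**What to change.** Add one sentence for TiC-P. Keep arithmetic mean costs and the arm-by-time contrasts, but estimate residual variance separately by arm, or use robust (sandwich) standard errors at patient level. Report direct medical costs and productivity costs separately, and put them on the same time basis if they are ever summed. The other instruments can keep the planned model.

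A bootstrap that resamples treatment groups is not recommended: at most six patients per group means about 54/6 = 9 control groups, and the individual arm has no groups to resample.

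The cost is a little programming and one extra model specification, with no new data. The interval against control becomes wider. Correcting k of 0.939 to 0.815 in the working means about 1/0.939 to 1/0.815, or 7% to 23%, when costs fall by 20-50%. The gain is nearly complete for the change contrast and smaller for the 9-month difference if costs are heavily skewed.

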### Procedure

Cooperating GPs and specialists are asked to give each eligible patient an invitational letter explaining the goal of the study and describing the interventions. The patient fills in the IBS questionnaire to confirm the diagnosis. If the patient is interested in participating in the trial, the GP or specialist hands the patient study information with the Informed Consent letter and a brochure from the government explaining the law and the rights of patients participating in medical research. After confirmation of the intention to participate, the patient is referred to the collaborating psychologist, either in the hospital or in primary care practice. The psychologist checks the in- and exclusion criteria and explains the study. If the patient is willing to participate, she/he signs the Informed Consent letter, completes the questionnaires and sends them, together with the IBS-criteria checklist in a reply-envelope to the investigator. After randomisation the patient is invited to the therapy she/he is randomised to.

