### Time line and follow-up

Enrolment started May 2011. The inclusion of patients will take approximately two years. After the active treatment period of 12 weeks, all patients will be followed for an additional period of 9 months, to assess the sustainability of the effects of the interventions. The primary outcome will be measured weekly during the first four weeks after finishing treatment and again weekly during four weeks 9 months post treatment. The secondary endpoints will be assessed prior to intervention, immediately after the intervention and at 9 months after finishing the intervention.

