#### Adjustment for confounders

In case of (unexpected) differences in relevant baseline characteristics between the three comparison groups, adjustment for the possible confounding effect of these differences will be performed in multivariate regression analyses.

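### As written, the repeated-measures model for the secondary scores gives week 0 its own arm difference and adjusts for baseline only if imbalance is seen; prespecifying baseline adjustment would gain precision at no cost

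*Protocol article*

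**What the plan says.** Four places in the protocol article bear on this.

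- **Uni- & bivariate analysis.** The adequate relief scores and the six secondary scores "will be estimated by time point of assessment and arm of randomisation using a statistical model for repeated measurements (preferably a random effects model", and "terms for interaction of {arm × time point} will be included in the statistical model". No baseline covariate is named, and no equality of arm means at week 0 is stated.
- **Time line and follow-up, and Table 1.** "The secondary endpoints will be assessed prior to intervention, immediately after the intervention and at 9 months after finishing the intervention". Table 1 labels its columns as time points. The first is week 0, and all six secondary scores are marked there, at week 12 and at week 52. Adequate relief has no week-0 entry.
- **Procedure.** The patient "completes the questionnaires and sends them, together with the IBS-criteria checklist in a reply-envelope to the investigator. After randomisation the patient is invited" to the allocated therapy. The baseline scores therefore precede randomisation.
- **Adjustment for confounders.** "In case of (unexpected) differences in relevant baseline characteristics between the three comparison groups, adjustment for the possible confounding effect" is to be made by multivariate regression. Neither the relevant characteristics nor the size of difference that triggers adjustment is defined.

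The Abstract also describes the secondary efficacy parameters as changes in these scores, so baseline is meant to enter the analysis somehow.

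**The concern.** Because week 0 is measured before allocation, the true arm means there are equal, and any observed difference is chance. If week 0 is nonetheless a time point with its own arm difference, the treatment effect can be read in two ways:

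- **(a)** as the arm difference at week 12 or 52, which ignores baseline and leaves the chance imbalance in the estimate;
- **(b)** as the arm × time term relative to week 0, which is a difference in change scores and over-corrects for that imbalance whenever the correlation is below 1.

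The random effect does not resolve this. With complete data and a full arm × time mean structure, the fitted values are simply the arm-by-time means.

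Two things are at stake. First, precision is lost on the scores that answer the stated secondary objectives. This matters most against the control arm, which has only 54 patients. Second, adjustment triggered by observed imbalance makes the reported model depend on the data. Readings (a) and (b) also differ by the whole of the observed baseline gap, and the article does not say which is the result.

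**Working it through.** **The plan's own figures.** The sample size section covers only the binary primary outcome. Its 135 per arm (57% response, 15-point margin, power 0.80) reproduces with one-sided alpha 0.05: (1.645 + 0.842)² × 2 × 0.57 × 0.43 / 0.15² ≈ 134.7, so 135. The 44 per arm for superiority comes out at 35.9 × 1.25 = 44.9, so 45, which is close. There is no planned figure for any secondary score.

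**Inputs from the article.** Randomised 150 + 150 + 54; after 10% loss, 135, 135 and 54 × 0.9 = 48.6, taken as 49. Cluster size 6 and intra-class correlation 0.05 give a design effect of 1 + 5 × 0.05 = 1.25.

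**Assumed inputs.** Equal SDs over time, the same correlation r between week 0 and a follow-up for every score, two-sided alpha 0.05, and a starting power of 80%.

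**Step 1: relative variance of the arm contrast at one follow-up** (units of SD², times 1/n₁ + 1/n₂).

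| r | (a) follow-up only: 1 | (b) change: 2(1−r) | baseline-adjusted: 1−r² |
|---|---|---|---|
| 0.3 | 1.00 | 1.40 | 0.91 |
| 0.5 | 1.00 | 1.00 | 0.75 |
| 0.7 | 1.00 | 0.60 | 0.51 |

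The adjusted variance never exceeds either alternative. It is 1 − r² ≤ 1, and 2(1−r) − (1−r²) = (1−r)² ≥ 0.

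**Step 2: power.** New power = Φ[(1.960 + 0.842) × √(old variance / new variance) − 1.960].

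- r = 0.5, from (a) or (b): 2.802 × √(1/0.75) − 1.960 = 1.275, so 89.9%.
- r = 0.3: from (a) 83.6%, from (b) 93.5%.
- r = 0.7: from (a) 97.5%, from (b) 86.0%.

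**Step 3: clustering.** If clustering comes from the therapy group or therapist, it is absent from scores taken before randomisation. At r = 0.5, adjustment then removes r² = 0.25 from a variance of 1.25. The ratio is (1.25 − 0.25)/1.25 = 0.80, and power is Φ(2.802 × √1.25 − 1.960) = Φ(1.172), about 88%.

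**Step 4: dependence on effect size, r = 0.5, no clustering.**

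| Effect (SD) | 135 v 135: unadjusted → adjusted | 135 v 49: unadjusted → adjusted |
|---|---|---|
| 0.2 | 37.6% → 47.5% | 22.3% → 28.3% |
| 0.3 | 69.3% → 81.2% | 43.6% → 54.7% |
| 0.4 | 90.8% → 96.7% | 66.9% → 79.1% |
| 0.5 | 98.4% → 99.7% | 85.0% → 93.3% |

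The gains run from 1.3 to 12.2 points.

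**Step 5: how often chance imbalance would matter.** At baseline, 150 v 54 gives a standard error of √(1/150 + 1/54) = 0.159 SD. A gap of at least 0.2 SD (z = 1.26) has about a 21% chance for each score.

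**The case against.** The strongest objection is that the article never says week 0 is a response. The same sentence covers adequate relief, which has no baseline measurement, so an arm × time term does not by itself put week 0 among the outcomes. A model of weeks 12 and 52 with a baseline covariate would also contain arm × time terms. The stated preference for a random effects model leaves the specification open, and a condensed article often leaves such detail to the full protocol or SAP.

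This stands to a degree: the model is inferred, not stated. The inference is still the natural one. Table 1 makes week 0 a time point for all six scores, no baseline term is named, and the article does state when baseline adjustment happens, namely only after differences are seen. That last rule is fixed in the text and is weaker than a prespecified term.

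A reader might go further, in three ways that the document does not support.

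- **That the plan has no baseline adjustment.** The section on confounders provides it, conditionally.
- **That the trial loses 10 points of power.** That figure needs a correlation of 0.5 and a starting power near 80%, neither of which is in the article. One correlation for six instruments, including costs, is itself a simplification. Nor does the 25% variance reduction carry over unchanged under the design effect of 1.25 if clustering starts after randomisation.
- **That the results would be biased.** Under randomisation, both unadjusted readings are unbiased.

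**Conclusion.** The point holds as a free improvement. Taken together, the article's sections imply an arm × time model with week 0 as a time point and adjustment only on observed imbalance. The secondary-score contrasts would be valid but less precise than the data allow, and the choice of model would depend on the data.

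The size is illustrative. At r = 0.5 the variance falls by about 25%, or about 20% with clustering that arises only after randomisation, and an assumed 80% power rises to about 88 to 90%. Over effects of 0.2 to 0.5 SD at that correlation, and without clustering, the gain is roughly 1 to 12 points. The direction does not depend on r under the equal-SD assumption, but the size does. The responder analysis and the sample size are untouched.

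**What to change.** In the section on uni- and bivariate analysis, state that for the six secondary scores the week-12 and week-52 values are the outcomes. The patient's own week-0 score and its interaction with time point enter as covariates, regardless of observed imbalance. Equivalently, keep all three time points in the model but constrain the arm means to be equal at week 0. Report the arm contrasts at each follow-up time from that model. In the section on confounders, add that its conditional rule does not govern adjustment for the baseline value of the same score.

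The cost is a sentence or two of analysis wording, with no new data, patients or staff.
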